### Quality control and quality assurance

Before the start of the study, in order to ensure the quality of the research, we will strictly review the recruited doctors, rehabilitation therapists, evaluators, and VR equipment, and take the following specific measures:
The recruited doctors should fully understand the experimental process;Train therapists to carry out VR-assisted rehabilitation training of subjects and how to deal with potential adverse events during the training;Train evaluators how to appropriately manage and process outcome indicators;Among the 38 subjects included, the data of the subjects who finally completed all the training programs shall be analyzed for completeness and quality; andConduct debugging of VR equipment and gait analyzer (data analysis equipment) so as to achieve the optimal running state of the equipment.

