**Methods:**

The study describes a prospective, randomized controlled clinical trial. Thirty-six stroke patients will be screened and enrolled as subjects within 1 month of initial stroke and randomized into two groups. The VRT group (*n* = 18) will receive VR-assisted training (30 min) 5 days/week for 3 weeks. The non-VRT group (*n* = 18) will receive functional gait rehabilitation training (30 min) 5 days/week for 3 weeks. The primary outcomes and secondary outcomes will be conducted before intervention, 3 weeks after intervention, and 6 months after intervention. The primary outcomes will include time “up & go” test (TUGT). The secondary outcomes will include MMT muscle strength grading standard (MMT), Fugal-Meyer scale (FMA), motor function assessment scale (MAS), improved Barthel index scale (ADL), step with maximum knee angle, total support time, step frequency, step length, pace, and stride length.

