### Randomization and blinding

The eligible participants based on the inclusion and exclusion criteria will be randomly allocated in a 1:1 ratio to either the VR training group and the non-VR training group. The attending physician will obtain the informed consent and refer the participants to the study coordinator after their baseline information has been assessed. The participants will be randomly assigned to the VR training group and non-VR training group by the study coordinator. A random allocation sequence will be generated in advance using a computerized random number generator by a biostatistician who will be not involved in this trial. The study coordinator who will be not involved in recruiting participants will keep the random list and will assign the treatment plans accordingly. The biostatistician and research coordinator will keep the random list until the end of the research to ensure that the assignment is blind to the participants and the attending physician who will recruit participants.

Although it is impossible to blind the participants and rehabilitation trainer due to this being a non-pharmacological intervention trial, the allocation will be blind to the outcome assessors and the data analyst. Participants will be instructed not to disclose the allocation to the attending physician and the outcome assessors.

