### Sample size calculation

The sample size calculations are based on the primary outcome measure, the TUGT scale [35]. It was estimated that a sample of 28 participants (14 per group) would provide 80% power (*α* = 0.05, *β* = 0.2) to detect a difference between group means of 3.16. A difference of 3.16 points on the TUGT scale is regarded as minimum detectible change [36] using the program PASS, which takes into account the number of sample groups and the number of evaluation measures. To reach this total number of individuals, at least 36 individuals must be recruited, allowing a dropout rate of 20%.

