### Safety

VR is an emerging technology and its related products have been gradually developed in recent years. To date, no relevant adverse events have been reported. In the process of training subjects’ gait recovery with VR technology; our research team will strictly follow the relevant regulations of the medical ethics committee to ensure the maximum safety and ethical protection of subjects. As VR technology is a relatively new technology, subjects may not be able to complete training tasks due to ineptness or intolerance (such as dizziness, nausea, sore eyes, disorientation) during training. Adverse events (e.g., falls, pain, and dizziness) that occur during the study period, whether or not related to the study intervention are registered. Considering the above two aspects, we will take the following measures to achieve the best training environment:
During the 3-week training, a strict training plan will be made for each subject on a weekly basis, adjusting the training schedule according to the actual conditions of the subjects;Pay close attention to the feedback and fitness of subjects using VR technology for rehabilitation training;Periodically evaluate the intervention effect of subjects using VR technology for rehabilitation training; andSupporting subjects’ decision to withdraw from the study.

This study will strictly comply with the requirements of clinical operation guidelines and internationally recognized legal requirements. Any adverse events will be reported directly to the ethics committee immediately, and the training regimen will be adjusted accordingly after each adverse event. There is no anticipated harm and compensation for trial participation.

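### The quality-control section counts 38 subjects where the trial has 36, and ties the data to be analysed to those who completed all training

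*Protocol article*

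**What the plan says.** The Quality control and quality assurance section lists, among its measures: "Among the 38 subjects included, the data of the subjects who finally completed all the training programs shall be analyzed for completeness and quality".

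On the number of patients:
- The abstract's Methods paragraph says: "Thirty-six stroke patients will be screened and enrolled as subjects within 1 month of initial stroke and randomized into two groups". It gives 18 to each group.
- The Sample size calculation section starts from 28 evaluable patients ("It was estimated that a sample of 28 participants (14 per group) would provide 80% power") and continues: "To reach this total number of individuals, at least 36 individuals must be recruited, allowing a dropout rate of 20" per cent.
- The Randomization and blinding section has participants "randomly allocated in a 1:1 ratio to either the VR training group and the non-VR training group".

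On whose data are used, three other sections bear on the question:
- Recruitment and consent: participants are asked whether their data may still be used if they withdraw.
- Outcome measures: every participant is to be measured at baseline, at 3 weeks and at 6 months.
- Statistical analysis: all collected data are to be processed in SPSS.

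On why training may not be completed, the Safety section warns, with reference to VR being new, that "subjects may not be able to complete training tasks due to ineptness or intolerance (such as dizziness, nausea, sore eyes, disorientation) during training".

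**The concern.** One sentence raises two problems.

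The first is a plain contradiction. 36 and 38 are both given as the number of patients in the same trial, so a reader cannot tell which denominator a later participant flow diagram should be held to.

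The second is the restriction to subjects who finished all training. Completion happens after randomisation. The Safety section foresees non-completion through ineptness or headset intolerance, and control patients wear no headset, so the reasons for stopping may differ between arms. If those who stop VR training also walk less well, leaving them out removes poor results from one arm only. The comparison would then describe patients who tolerate VR and no longer the effect of assigning VR. With about 18 patients per arm, a few selective exclusions can move the result.

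If the sentence is only a data-quality check, the problem is smaller but remains: a completeness check confined to completers passes over the patients most likely to have gaps.

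**Working it through.** **1. The plan's own number.** Inputs from the Sample size calculation section: 14 evaluable per group, 20% dropout.
- Per arm: 14 / (1 − 0.20) = 17.5, rounded up to 18. Total 2 × 18 = 36. The stated figure is reproduced and matches the abstract's 18 + 18.
- From the total: 28 / 0.80 = 35, which becomes 36 with equal arms.
- Multiplying instead of dividing: 28 × 1.2 = 33.6, so 34. This does not give 38 either.

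**2. What 38 would need.** 1 − 28/38 = 26.3% dropout, against the stated 20%. At 20% dropout, 38 patients leave 30.4 evaluable and 36 leave 28.8. Only 36 fits the planned 28.

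**3. The passages side by side.**

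| Section | Whose data |
|---|---|
| Quality control and quality assurance | those who completed all training |
| Outcome measures | all participants, at each of three times |
| Recruitment and consent | withdrawn participants too, if they agree |
| Statistical analysis | all data collected |

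The first row is narrower than the other three. If it defines the analysis set, it conflicts with them. If it is a data check, there is no conflict over the efficacy set, but the check covers too few subjects.

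**4. Size of a bias if completers alone were analysed.** The documents give no SD and no expected pattern of loss, so these are assumptions.
- SD: a two-sample t test with 14 per group, a difference of 3.16, 80% power and α = 0.05 implies an SD of 2.87 if two-sided and 3.27 if one-sided. The section does not state which.
- Severe case: the VR non-completers are exactly the worst 20% on a normally distributed TUGT, and controls lose none or lose at random. Mean shift = φ(0.842) / 0.80 = 0.280 / 0.80 = 0.350 SD. In seconds: 0.350 × 2.87 = 1.0 (1.1 at SD 3.27). Relative to the target: 1.0 / 3.16 = 32%.
- Milder case: dropping out correlates 0.5 with outcome. Shift = 0.5 × 0.350 = 0.175, about 0.17 SD, or 0.5 s at SD 2.87.
- False rejection of a true null, nominal two-sided 5%, noncentral t, 14 VR patients against 14 to 18 controls: 14.5% to 15.8% in the severe case and 7.3% to 7.6% in the milder one.

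**5. A second way to see the range.** If k of 18 VR patients are dropped and their mean TUGT is worse than that of VR completers by D, the VR mean shifts by (k/18) × D. For k = 2, D = 3.16 this is 0.35; for k = 4, D = 10 it is 2.2. Both k and D are assumed.

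**The case against.** The strongest reply is that the sentence does not define an efficacy population. It is one item in a quality-assurance list, next to evaluator training and equipment debugging, and what it prescribes is an analysis for completeness and quality. It names no group comparison. This stands: a reader might infer that the trial will analyse completers only, but the text does not establish that. Nor is it the only text on whose data are used, since the consent, outcome and statistics sections point to wider use.

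A reader might also look for support in the sizing on 28 of 36 or in the planned t tests. Neither helps. Dropout inflation allows for missing outcomes and is neutral about the analysis set. A patient who stops training but attends the 3-week visit supplies a full before-and-after pair, and the between-group test is an independent-samples test that needs no pairs.

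Nor do the documents show that exclusions would favour VR. The Safety section says only that patients may fail to complete, and sets out adjustments to prevent it. The Discussion expects VR to lower dropout, so loss could be greater among controls. Nothing in the documents ties dizziness or nausea to poor TUGT.

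Finally, naming an analysis set or a model for incomplete data can belong to an analysis plan that is not shown, so their absence is no fault here.

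Two things survive. The 38 is inconsistent on any reading; a target of at least 36 leaves room for a few more patients, but the abstract fixes 18 per arm. And the restriction to completers is unsuitable on either reading: as an analysis set it excludes patients after randomisation, and as a data check it misses those most likely to have incomplete data.

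**Conclusion.** The point holds in two parts. The count of 38 is an error or is unexplained: the stated inputs give 36, and 38 would need about 26% dropout. It enters no calculation, so the planned power is unaffected. The completer wording is ambiguous, and both available readings need correction.

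Bias is a risk that depends on how the sentence is applied. It arises only if the wording is used as the efficacy set, loss differs between arms and loss is related to TUGT. Under those conditions it is about 0.35 SD in the severe case and about 0.17 SD in the milder one, with false rejection near 15% and 7% respectively. The conversion to seconds also rests on an SD solved back from the sample size under a two-sided test. The documents do not support a firm statement that the trial will overstate the effect of VR.

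**What to change.** Change 38 to 36, or explain where 38 comes from. Replace the sentence with: *Data of all randomised participants will be checked for completeness and quality and analysed in the group to which they were allocated, whether or not training was completed; the scheduled T1 and T2 assessments will be sought from those who stop training unless they refuse.* Any analysis of completers should be labelled supportive only.

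The cost is mainly wording, because the Outcome measures section already schedules these visits for every participant. The estimate may be somewhat smaller than among completers. The change should be made before the data are analysed. A likelihood-based model using T1 and T2 together would let partial data contribute, but it is optional and the correction does not depend on it.

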### Others

The steering committee consists of the authors [name], [name], [name], [name], [name], [name], and [name]. All members are independent of the sponsor. The committee members participate in designing the study and supporting the on-going trial with advice. There is a data safety monitoring board which is independent of the sponsor, including statisticians and a chairman who is [name]. An audit may be performed by the medical supervision and management department to evaluate clinical study conduct and compliance with the protocol, SOPs, GCP, and the applicable regulatory requirements.

### Protocol amendments

We will discuss the protocol amendments in the Scientific Board and notify the sponsor and funder first. A copy of the revised protocol will be sent to the PI. Any deviations from the protocol will be fully documented using a breach report form.

### Dissemination plans

The datasets analyzed during the current study are available from the corresponding author on reasonable request. Trial data and results will be published in scientific journals. The consent form and trial information materials are available from the corresponding author on request.

## Discussion

In this study, the effects of immersive VR technology on gait rehabilitation of stroke patients will be evaluated after 3 weeks of intervention and at a 6-month follow-up. The improvement of traditional gait-disorder rehabilitation for stroke patients is required as the traditional method is time- and resource-consuming and relatively one-dimensional with regard to the patient experience. The effectiveness and feasibility of the newly developed VR technology in rehabilitation training could provide key solutions to these limitations. The main purpose of the proposed study protocol is to establish an immersive VR gait rehabilitation training experience and comparatively evaluate outcomes in a controlled, randomized experiment.

VR technology leverages interactive simulations to create an environment that is similar to the real-world scenarios. Stroke patients can complete tasks as required and interact with virtual objects. Previous studies have pointed out that such human-computer interactions should be easy to adapt, be intuitive and convenient to use, and allow the subjects to readily transfer the skills learned in the virtual environment to real life. In addition, VR can provide immediate motor feedback during training, allowing for task-oriented repetitive exercises while enabling changes to the traditional treatment patterns which can feel repetitive or boring for patients. In the form of a virtual game, the treatment of patients with lively and interesting scenes and training projects allows patients to feel more relaxed, engaged, and therefore more invested in the active participation. The real-time feedback can additionally provide patients with a greater awareness of their training and performance [37]. In addition to repetitive training, the modulation of different environments during a VR-assisted training session can also be very helpful for patients’ learning ability, which can enhance the ability of patients to adapt to the environment and thus improve their sports learning ability [3, 38]. This mode of higher participation can ultimately improve the enthusiasm and acceptance of training for patients, reducing the dropout rate and enabling patients to maintain long-term rehabilitation [39]. Moreover, studies have shown that immersive VR is feasible in the rehabilitation of stroke patients with gait disorder [20]. Interestingly, one study has found that subjects receiving occasional intermittent treatment were more effectively impacted than others receiving daily treatment [40].

## Trial status

The study is actively recruiting participants. The end of the trial phase and subsequent data analysis are expected to be completed within 24 to 36 months. The protocol version number is 4.0. Recruitment started on December 1, 2019, and will close on December 1, 2022.

## Data Availability

Study data can be provided on request. For interested researchers, please contact [name].

## Abbreviations

VR: Virtual reality
TUGT: Time “up & go” test
MAS: Motor assessment scale
HMD: Helmet display
ADL: The ability of daily living activities
